### Processes and interventions

Table 1 shows the complete schedule of assessments that will be performed during this study. We describe the procedures that will be performed at each visit in further detail below.

**Table 1 Tab1:** Schedule of study procedures. This chart shows all possible visits for each cohort and assessments that would be expected to take place for each participant in each cohort. Visits marked with * may not take place for all participants

Visit	Elective cohort				Emergency cohort				Medical cohort		
	A	B	C	D	A*	B	C	D	B	C	D
**Demographics, observations, medications, medical history, blood tests as part of routine care**	**✓**	**✓**	**✓**		**✓**	**✓**	**✓**		**✓**	**✓**	**✓**
**Review of CT scans performed as part of routine clinical care (if available)**	**✓**				**✓**						
**BATT using ultrasound**	**✓**	**✓**	**✓**	**✓**	**✓**	**✓**	**✓**	**✓**	**✓**	**✓**	**✓**
**BIA**	**✓**	**✓**	**✓**	**✓**	**✓**	**✓**	**✓**	**✓**	**✓**	**✓**	**✓**
**Handgrip strength**	**✓**	**✓**	**✓**	**✓**	**✓**	**✓**	**✓**	**✓**	**✓**	**✓**	**✓**
**Short Physical Performance Battery**	**✓**			**✓**				**✓**	**✓**	**✓**	**✓**
**Gait speed alone**			**✓**				**✓**				
**Physical function by PROMIS**	**✓**		**✓**	**✓**	**✓**		**✓**	**✓**	**✓**	**✓**	**✓**
**Katz ADLs and Lawton IADLs**	**✓**		**✓**	**✓**	**✓**		**✓**	**✓**	**✓**	**✓**	**✓**
**Mini Nutritional Assessment (Full)**	**✓**			**✓**	**✓**			**✓**	**✓**		**✓**
**Extra frailty assessments**	**✓**		**✓**	**✓**	**✓**		**✓**	**✓**	**✓**	**✓**	**✓**
**Venepuncture (optional)**	**✓**	**✓**			**✓**	**✓**			**✓**		
**Application of physical activity recorder (optional)**		**✓**				**✓**			**✓**		
**Delirium assessment**		**✓**	**✓**		**✓**	**✓**	**✓**		**✓**	**✓**	
**Fluid balance assessment**		**✓**	**✓**		**✓**	**✓**	**✓**		**✓**	**✓**	
**Participant feedback**				**✓**				**✓**			**✓**

*PROMIS* Patient Reported Outcome Measures Information System, *ADLs* Activities of Daily Living.

Visit A: Preoperative assessment; in preoperative assessment clinic for elective cohort, on ward prior to surgery for emergency surgery cohort (where possible) – not applicable to medical cohort.

Visit B: Immediate; Within 48 h of surgery for surgical cohorts, within 48 h of admission for medical cohort.

Visit C: One week; 7 (+/− 2) days after surgery (surgical cohorts) or after admission (medical cohort).

Visit D: Three months; 13 (+/− 1) week after surgery (surgical cohorts) or admission (medical cohort).

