### Design and setting

This is a single site cohort study at the Queen Elizabeth Hospital Birmingham (QEHB), involving 56 elective colorectal, 56 emergency abdominal surgery, and 56 medical patients. QEHB is a large tertiary hospital, with a firmly embedded research infrastructure. In the elective cohort, measurements will be performed in preoperative assessment clinic, within 48 h of surgery, at 7 days postoperatively (+/− 2 days), and at 13 weeks postoperatively (+/− 1 week). In the emergency surgery cohort, we aim to recruit participants preoperatively where possible. Where this is not possible, we will recruit participants within 48 h of emergency surgery; further assessments will be performed at 7 days postoperatively (+/− 2 days), and at 13 weeks postoperatively (+/− 1 week). Medical patients will be recruited within 48 h of admission with further assessment at 7 days post-admission (+/− 2 days), and at 13 weeks post-admission (+/− 1 week). The timeframe of 13 weeks has been chosen pragmatically as a timeframe that was considered important to our patient and public involvement panel that could be feasibly conducted without high drop-out rates. The full study schema is shown in Fig. 1.

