### Physical function – patient reported outcome measures information system (PROMIS®)

PROMIS physical function is a validated measure of physical function [39, 40]. PROMIS is an initiative that compares participant responses to a reference population and derives a T-score, where 50 is the mean, and 10 is the standard deviation. PROMIS will be measured at baseline and 3 month follow-up for all groups. The raw scores will be entered into the HealthMeasures scoring service, powered by Assessment Center^SM^ to derive T-scores.

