### Data analysis

Data analysis will be conducted using IBM SPSS® Version 22. Results for each cohort will be analysed separately, although secondary data analysis will be conducted on all groups together. Interim analysis is planned with involvement from a patient and public involvement panel. Outcomes will be summarised at baseline, 7 days postoperatively, and 13 weeks postoperatively. The data analysis of the primary research question will include the following models:
Unadjusted model with PROMIS at 13 weeks as the outcome of interest, and the secondary outcome as the covariate of interest (i.e. change in BATT, handgrip strength and/or gait speed from baseline to 7 days).Adjusted model with PROMIS at 13 weeks as the outcome of interest, and the secondary outcome as the covariate of interest (i.e. change in BATT, handgrip strength and/or gait speed from baseline to 7 days), with adjustment for the baseline PROMIS score, and patient demographics (e.g. age, gender).Model with PROMIS at 13 weeks as the outcome of interest, with adjustment for baseline PROMIS, and all secondary outcomes as covariates to establish the strength of association between those secondary outcomes and the primary outcome. This model will be used to establish which of the secondary outcomes (i.e. change in BATT, handgrip strength and/or gait speed from baseline to 7 days) is most strongly associated with change in PROMIS at 13 weeks.

Change in PROMIS rather than change in SPPB, which can be considered an objective measure of physical function, has been selected as our primary outcome for two reasons. Firstly, our patient and public involvement panel considered their own perception of their physical function to be most important. Although perception of function may differ from objective function, how function is perceived for them as individuals was considered more important. Secondly, it will only be possible to obtain true pre-hospitalisation measures of SPPB for the elective cohort. PROMIS provides a method of evaluating physical function prior to admission in the emergency cohorts. Change in SPPB will be evaluated as a secondary outcome in the elective cohort.

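### Table 1 contradicts the text on baseline PROMIS in the emergency surgery cohort: patients recruited after surgery have none scheduled, although the primary outcome and two of the three models need it

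*Protocol article*

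**What the plan says.** **The schedule.** Processes and interventions introduces the table with "Table 1 shows the complete schedule of assessments that will be performed during this study". In the row "Physical function by PROMIS" the ticks are:

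- elective cohort: A, C, D
- emergency cohort: A*, C, D (B is blank)
- medical cohort: B, C, D

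The rows for Katz and Lawton activities of daily living, the Mini Nutritional Assessment (MNA) and the extra frailty assessments are likewise blank at emergency Visit B and ticked at medical Visit B. The asterisk on emergency Visit A is explained by "Visits marked with * may not take place for all participants".

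**Recruitment.** Design and setting aims for preoperative recruitment in the emergency surgery cohort, then adds: "Where this is not possible, we will recruit participants within 48 h of emergency surgery". For those patients Visit B is the first visit.

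**The text on baseline.** The PROMIS section states "PROMIS will be measured at baseline and 3 month follow-up for all groups". Nutritional assessment places the MNA at baseline visits in each group, and Frailty assessment starts at the first visit.

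**The use made of it.** Data analysis says "Change in PROMIS rather than change in SPPB, which can be considered an objective measure of physical function, has been selected as our primary outcome" and gives as one reason that "PROMIS provides a method of evaluating physical function prior to admission in the emergency cohorts". Of its three models, the second and third adjust for baseline PROMIS. The first is described as "Unadjusted model with PROMIS at 13 weeks as the outcome of interest" and uses no baseline PROMIS.

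**The concern.** A schedule described as complete is what ward staff are likely to work from. For an emergency patient recruited after surgery, it asks for no PROMIS until Visit C, 7 (+/- 2) days after the operation. A current-function score at that point is a post-insult measurement and cannot serve as the baseline.

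Three analyses then lose these patients: change in PROMIS, and the second and third models. Part of the stated case for PROMIS over SPPB is that it can reach back to function before admission in patients who arrive as emergencies. The table withholds it at entry from emergency patients who could not be seen before surgery.

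The text does not fully close the gap either. It promises a baseline but names no visit and no reference period for patients recruited after surgery. A PROMIS taken at Visit B about current function would describe the first 48 h after emergency abdominal surgery, not the state before admission.

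**Working it through.** **1. Is the blank cell a reading error?** The four affected rows, early visits only:

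| Row | Elective A | Elective B | Emergency A* | Emergency B | Medical B |
|---|---|---|---|---|---|
| PROMIS | yes | – | yes | – | yes |
| Katz/Lawton | yes | – | yes | – | yes |
| MNA | yes | – | yes | – | yes |
| Frailty | yes | – | yes | – | yes |

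The pattern is the same in all four rows, so a shifted column in one row is not the explanation. Emergency B has the same blanks as elective B. In the elective cohort these do no harm, because Visit A carries no asterisk. The medical cohort has no Visit A and has all four items at B. What is missing is a fallback when emergency Visit A is skipped.

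**2. The plan's own sample size.** Inputs from Power calculation: PROMIS change 6, SD 10, 80% power, 5% significance (bidirectional), paired t-test, 45 evaluable from 56.

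SD of change = 10 × √(2(1 − r)), where r is the correlation between the two PROMIS scores.

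- r = 0: SD of change = 14.14, standardised change 6/14.14 = 0.424, required n = 45.6, power at 45 = 79.5%.
- r = 0.5: SD of change = 10, standardised change 0.6, required n = 23.8, power at 45 = 97.6%.

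The stated 45 is therefore reproduced, to within one patient, at zero correlation.

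**3. Effect of following the table.** Let q be the share of emergency patients whose first visit is B. The document gives no value, so q is an assumption. Assume also that loss to follow-up does not depend on recruitment route. Patients with a baseline = 45 × (1 − q).

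| q (assumed) | With baseline PROMIS | Power, r = 0 | Power, SD of change 10 |
|---|---|---|---|
| 0% | 45 | 79.5% | 97.6% |
| 25% | 33.75, taken as 34 | 67% | 92% |
| 50% | 22.5, taken as 22 | 48% | 77% |
| 75% | 11.25, taken as 11 | 25% | 44% |

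**4. Sensitivity to the base.** A 25% loss from 56 leaves 56 × 0.75 = 42, not 45; that is a separate matter. Starting from 42, the counts are 32, 21 and 10, with power 64%, 46% and 23% at r = 0, or 91%, 74% and 40% with SD of change 10. The picture is the same.

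**5. Scope of these figures.** They are for the paired t-test on change in PROMIS within the emergency cohort. The second and third models are regressions of 13-week PROMIS on early changes in muscle measures. The patient counts carry over to them as an upper limit, but the power figures do not.

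**The case against.** The strongest reply is that the text already commits to the measurement. The PROMIS section covers all groups, the MNA and frailty sections cover baseline or first visit, and Data analysis relies on PROMIS for pre-admission function. Table 1's caption says that it charts all possible visits, and the procedures are described in more detail after it. On that view the baseline items sit under A* because it is the first column, and the defect is a missing footnote.

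Much of this stands. A reader might infer that the primary outcome cannot be computed for patients recruited after surgery, or that the investigators chose to do without their baseline. The document supports neither inference: data are lost only if the table is followed over the text.

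Two other inferences also go too far. One is that the patients left would be the more stable ones. Selection is plausible, but the article does not say why preoperative recruitment might fail. The other is that the medical cohort's Visit B PROMIS is already worded for function before admission; Table 1 shows only a tick.

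Nor is there any basis for assuming that most emergency patients enter after surgery. The stated aim is preoperative recruitment where possible, so low shares belong in the range.

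The reply does not remove the contradiction. The table is presented as complete, and the text does not say when, or about what period, a patient recruited after surgery answers PROMIS.

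**Conclusion.** The point holds as a contradiction between schedule and text that bears on the primary outcome. If Table 1 is followed, emergency patients recruited after surgery have no baseline for change in PROMIS or for the second and third models. The first model and the 13-week score are untouched, and so are the other two cohorts.

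The size depends on an unstated share. At an assumed 25%, power falls to 67% on the zero-correlation basis that reproduces the plan's 45, but stays at 92% if the SD of change is 10. At 50% it is 48% or 77%, and at 75% it is 25% or 44%. If a pre-admission baseline is taken at the first visit from everyone, as the text intends, nothing is lost and the planned 45 stands.

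It should be corrected because a component of the primary outcome is at risk, the remedy is small, and a missed baseline can later be recovered only through longer recall.

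**What to change.** 1. In Table 1, add PROMIS, Katz/Lawton, MNA and the frailty assessments at emergency Visit B, with a footnote that they apply if Visit A did not take place.
2. In the PROMIS section, state that baseline PROMIS in patients recruited after admission refers to function before admission, and name the visit at which it is taken.
3. Where a baseline has already been missed, collect pre-admission PROMIS by recall at the next contact and flag it in the data. This is a different question from the current-function PROMIS scheduled at Visit C, and the two scores should be recorded separately.

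The cost is a minor amendment to the schedule, a few minutes of questionnaire at a visit that already takes place, and some recall error in reports given after surgery. The recall error is greater for any baseline collected late, which is the reason for the flag.

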### Muscle quantity assessment

#### Quadriceps ultrasound

Rectus Femoris (RF) and Vastus Intermedius (VI) muscles in both legs will be assessed using two-dimensional B-mode ultrasonography with a linear probe, as previously described [11]. This will be performed at first visit, immediately postoperatively (where applicable), at 7 day follow-up, and at 13 week follow-up. Participants will be positioned semi-upright with knees resting at 10–20° and advised to relax their muscles. The distance from greater trochanter to knee lateral joint line will be recorded and a mark placed on the skin mid-way between the two points. Measurements will be taken in line horizontally with these marks. Contact gel will be applied. Muscle thickness will be measured with the probe in transverse position. Depth will be adjusted until the femur and overlying structures are visible. The probe will be positioned such that the widest area of the RF appears over the midpoint of the femur. Frozen images at this location will be taken with the probe held in maximal relaxation.

Thickness measurements of subcutaneous tissues (SC), RF, and VI in a vertical line will be recorded, not including the fascia. Three frozen images will be used for all patients; a further image will be taken if there is greater than 10% variability between measurements. The mean of each reading will be used for analysis. BATT will be calculated as total thickness of right VI + right RF + left VI + left RF. BATT: SC ratio (BATT-SCR) will be calculated as BATT divided by total thickness of right SC + left SC [24]. Where possible, cross-sectional area of the right and left RF will be measured. All measurements will be performed by an investigator with training in taking these measurements. The reliability of BATT has been shown to be excellent when using the same protocol and same machine (intraclass coefficients > 0.9 for both intra-rater and inter-rater variability) [11].

A further image will be taken in the longitudinal position at each visit. Images will be saved and downloaded for assessment. RF and SC echogenicity will be determined using grey-scale analysis on Image J software. Pennation angle will be measured by the angle of insertion of the fascicles within the VI to the deep aponeurosis. The mean measure from up to three fascicles measured on each image will be used for analysis [29].

#### Bioelectrical impedance analysis (BIA)

BIA measurements will be taken at the first visit, immediately postoperatively (where applicable), at 7 day follow-up, and at 13 week follow-up using a multi-frequency analyser; Bodystat Quadscan 4000. This will not be performed if the participant has an implanted permanent pacemaker or defibrillator. The participant will be positioned lying semi-upright with knees resting in extension on the examination couch, hospital bed or equivalent. The assessor will ensure that limbs are not touching. Two electrodes will be placed on the right foot; one below the base of the toes and the other on the ankle between the medial and lateral malleoli. The red alligator clip will be attached to the electrode nearest the toes and the black to the one at the ankle. A further two electrodes will be placed on the right hand; one behind the knuckles and the other on the wrist next to the ulnar head. The red alligator clip will be attached to the electrode nearest the fingers and the black to the one at the wrist. Electrodes will be placed transversely so that the non-stick electrode connector is facing the researcher. The Bodystat Quadscan 4000 includes a quality control feature; an impedance graph is displayed prior to results being displayed. If the graph shows a smooth curve, the investigator will proceed to record results. If there are any bumps in the graph, the investigator will recheck lead and limb position prior to repeating the analysis. Single measurements will be recorded at each visit.

All returned measures including prediction marker, impedance, resistance, reactance, phase angle, fat weight, lean weight, dry lean weight, Fat Free Mass Index (FFMI), Body Fat Mass Index (BFMI), total body water, extracellular water, and intracellular water will be recorded. Skeletal muscle mass (SMM) will be additionally estimated using three previously validated equations: 1) SMM = 0.566 x Fat Free Mass (lean mass) [30]; 2) SMM = [((height^2^/ resistance) × 0.401) + (sex × 3.825) + (age x − 0.071)] + 5.102. In the second equation, height is in cm, for sex male = 1, female = 0, and age is in years [31]. 3) SMM = − 3.964 + (0.227 x (height^2^/ resistance)) + (0.095 x weight) + (1.384 x sex) + (0.064 x reactance) [32]. For all equations, the skeletal muscle index (SMI) will be calculated through the formula SMI = SMM/ height^2^_,_ where height is in m, for comparison with normative populations [33]. Height and weight are recorded for all patients at the site of this study as part of routine clinical care. For the elective cohort, height will be measured in preoperative assessment clinic using a stadiometer. For the emergency surgery and medical cohorts, height will be recorded using a stadiometer where possible. Where this is not possible, height will be taken from previous clinical records if these are available, or from patient report. If none of these methods are possible, then height may be estimated by measuring ulna length and conversion as per British Association of Parenteral and Enteral Nutrition guidelines [34]. If an estimate has been used, this will be recorded. The same height will be used for all visits.

#### L3-CT using imaging performed during routine medical care

CT scans will be reviewed if these have been performed as part of routine care and are available. Skeletal muscle index will be calculated at the level of the third lumbar vertebra (L3) on the first image with both vertebral spines visible using local hospital site Picture Archiving and Communication Software. This will be calculated by manually identifying skeletal muscles and automatic calculation of cross-sectional area; this value will be corrected for height^2^ [35]. Total psoas area (TPA) will also be calculated on the same slice. The right and left psoas muscle borders will be manually outlined and TPA will be calculated within the selected area. This measurement will be corrected for height^2^ [36]. This will be performed by the investigating geriatrician who is trained in use of the software.

### Muscle function assessment

#### Muscle strength

Handgrip strength will be measured at first visit, immediately postoperatively (where applicable), at 7 day follow-up, and at 13 week follow-up using a Jamar handheld dynamometer. Where the participant can sit in a chair, handgrip strength will be measured with the elbow flexed at 90^O^ and the forearm supinated. If measurements are taken in the bed this will be recorded; measurements will instead be performed in the most feasible upright position. Participants will be asked to “squeeze as hard as [they] can”. Handgrip strength will be measured twice on each side and the highest recording of the four measurements will be used for analysis [37].

#### Physical performance

The Short Physical Performance Battery (SPPB) is a standardised measure of physical performance that has been shown to be sensitive to change and provides an objective measure of physical function [38]. SPPB consists of usual gait speed, side-by-side stand, semi-tandem stand, tandem stand, and five chair stands (as quickly as they can). A total score of 12 is derived, with a lower score representing reduced physical performance. The SPPB will be measured at baseline and 3 month follow-up for the elective cohort, at 3 month follow-up for the emergency surgery cohort, and at all visits for the medical cohort. Gait speed alone will be measured at 7 day follow-up for both surgical cohorts. Gait speed will be measured by asking the participants to walk a four metre course at their “usual pace”. Gait speed will not be performed at recruitment in the emergency surgery cohort as this is considered unfeasible due to pain and immediate operative recovery. Measuring chair stands at 1 week post-operatively would cause increased abdominal strain, therefore, gait speed alone will be measured at this timepoint.

### Physical function – patient reported outcome measures information system (PROMIS®)

PROMIS physical function is a validated measure of physical function [39, 40]. PROMIS is an initiative that compares participant responses to a reference population and derives a T-score, where 50 is the mean, and 10 is the standard deviation. PROMIS will be measured at baseline and 3 month follow-up for all groups. The raw scores will be entered into the HealthMeasures scoring service, powered by Assessment Center^SM^ to derive T-scores.

### Comprehensive geriatric assessment

#### Demographics and comorbidities

Participant demographics, observations, medications, medical history, smoking and alcohol history, and blood test results performed as part of routine care will be collected. Medical comorbidities will be used to derive the Geriatric Index of Comorbidity [41]. Number of admissions and falls over the previous year will be recorded. Falls will be recorded from participant report. Any new information including changes in weight, observations, medications, or blood tests will be recorded at each visit, dependent on when these are recorded as part of usual clinical care.

